### Signs indicating DCD – Developmental Coordination Disorder Questionnaire (DCDQ)

The DCDQ [27] will be used with parents/caregivers of the children, who will fill in the questionnaire before they begin the treatment and also after the end, seeking to verify possible changes in parents’ perception about the motor characteristics of the children. We expect that the parents will fill the DCDQ in about 10–15 min.

### Anthropometric measurements

On the same day of the MABC-2 pre-test evaluation, anthropometric data about BMI (Body Mass Index), body fat percentage (BF%) and waist circumference (WC) of the children will be collected. Weight measurements for BMI will be made with a portable digital W602 (WISO®) scale, and height will be measured with a portable Wood (WCS®) stadiometer.

BMI will be calculated through the height/weight relation [29]. To calculate the BF% of the children, measurements around triceps and the subscapular skinfold will be done with a Lange® adipometer. Waist circumference will be measured in the narrowest region between the last rib and the umbilicus with a Sanny® metric tape. All anthropometric measurement collection procedures will be done in the observance of the techniques standardized by the literature. The anthropometric measurements will be performed in about 10–15 min.

### Motivation – Enjoyment Scale

At the end of the last session, the perception of satisfaction with each one of the activities and with the intervention as a whole will be assessed for each child through the Enjoyment Scale, an adapted scale by Jeslma et al. [20] translated to Portuguese. The score is expressed by the number of smileys, ranging from 0 (no fun at all) to 4 (super fun). Using this scale, each therapist will have direct results about the impact that the activities and the treatment as a whole had on each child. The Enjoyment Scale will be performed in about 5 min.

### Ethical approval

The respective research project of the present intervention protocols was approved by the Human Research Ethics Committee of the Universidade Federal de São Carlos (CEP/UFSCar), São Carlos, São Paulo, Brazil, with CAEE approval number 47091115.0.0000.5504. This project will be carried out according to the 466/12 Resolution of Conselho Nacional da Saúde (National Health Council), Brazil, and will follow the ethical principles of the Helsinki Declaration. All parents/caregivers will sign the Free and Clarified Consent Term, and the children the Consent Term, being aware of the research aims and procedures and the voluntary participation in the research. According to the Brazilian Ethics Statements, parents and children can stop the training anytime, without any punishments. This clinical trial is registered in the Registro Brasileiro de Ensaios Clínicos (REBEC), www.ensaiosclinicos.gov.br (RBR-89YDGJ); registration date 5 January, 2016, 11:42 p.m. (Brazilian time), last update 21 October 2016, 4:53 p.m. (Brazilian time), version number 1.

### Sample size

Sample size was calculated using the G*Power Software (3.1.9.2 version, Germany) based on a pilot study (*n* = 6). The calculation was performed considering the within-group comparisons for the Wii group, a power of 80%, and an alpha of 5%. The MABC total score assessed before and after 12 sessions was considered the main outcome and then considered for the analysis. The effect size was 0.80 (baseline: 58.0 ± 8.7; post 12-session intervention: 65.5 ± 9.9). Therefore, a sample of 15 participants was required for each group. In order to account for possible dropouts, we increased the sample to 16.

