### Randomization

Children will be randomly distributed by draw into one of the two training groups within a week at most after MABC-2 assessment. In case the draw leads to a sequence of four children in the same treatment group, the following four will be automatically allocated in the other. Once the distribution of blocks of four children is equalized, a new draw will be done for the following children to be randomly distributed. A person not involved with the study will receive a list of all children and will write in one piece of paper the term “Wii” and in another piece of paper the term “no-Wii.” This person will fold each piece of paper and will request to another collaborator not involved in this study to choose between the two papers. Then, following this draw, each child will be allocated into Wii or the no-Wii intervention group.

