## Discussion

This study protocol is the first to directly compare the efficacy of two motor-training protocols in children with DCD. The protocol is based on the domains of the MABC-2 domains. Various studies have already demonstrated the efficacy of intervention programs based on VR for these children [19–24, 31–36], but the absence of further protocol systematization has been an important hindrance for professionals and researchers in this field to clearly understand the impact of such interventions on children’s activity performance.

Studies comparing interventions based on VR and conventional interventions [19, 22–24] are scarce, and their results tend to demonstrate that despite the benefits of VR, conventional interventions seem to be more effective in the improvement of motor performance of children with DCD [19, 22–24]. Due to limitations and differences between the protocols adopted, though, these results must be interpreted carefully. Hence, when testing the efficacy of these two type of intervention programs, planned in similar manner, with similar scoring systems and activities, it will be possible to enhance evidence about the benefits in motor performance and learning of one program over the other.

One documented advantage of VR training, such as the Wii intervention, is the motivating aspects because the projected architecture on the environment of VR is capable of hold the children’s attention, being an important aspect for rehabilitation of children with DCD [20].

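### The sample size and its 80% power belong to a pre-post change inside the Wii arm, not to the Wii versus no-Wii comparison that the trial is run to make

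*Protocol article*

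**What the plan says.** The Sample size section of the protocol article bases the calculation on one arm: "The calculation was performed considering the within-group comparisons for the Wii group, a power of 80%, and an alpha of 5" per cent. The outcome is a pre-post contrast: "The MABC total score assessed before and after 12 sessions was considered the main outcome and then considered for the analysis". The inputs come from a pilot of six children: "The effect size was 0.80 (baseline: 58.0 ± 8.7; post 12-session intervention: 65.5 ± 9.9". From this the article concludes: "Therefore, a sample of 15 participants was required for each group", and then: "In order to account for possible dropouts, we increased the sample to 16".

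The rest of the article describes a comparison between arms. The Abstract and the end of the Background present a randomised trial comparing two training programmes. Under Randomization, "Children will be randomly distributed by draw into one of the two training groups". Statistical methods plans comparisons between groups, by ANOVA and ANCOVA if the data are parametric and by the Mann-Whitney test otherwise. The Discussion expects that "it will be possible to enhance evidence about the benefits in motor performance and learning of one program over the other".

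**The concern.** The calculation answers whether children improve over 12 Wii sessions. The trial asks whether they improve more, or less, than children in a matched active programme. These are different parameters with different variances. The number needed for the first does not carry over to the second by recruiting the same number into another arm.

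The effect size is also of the wrong kind. A gain of 7.5 points in a single uncontrolled group may include practice on the test, normal development and regression to the mean, as well as any effect of training. It says nothing directly about the difference between the programmes. The comparator trains the same three domains for the same time, so it may well produce a gain of its own.

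What is at stake is how the main result is read. If the between-arm test is not significant, a reader who sees 80% power and a required number per group could take the result as adequately powered evidence that the programmes are equally good.

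**Working it through.** **Inputs from the Sample size section.** Power 80%, alpha 5%, effect size 0.80, baseline 58.0 (SD 8.7), post 65.5 (SD 9.9), 15 per group raised to 16. I read the 16 as per group. Sidedness is not stated.

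**Step 1: the effect size.** Mean change = 65.5 − 58.0 = 7.5. Pooled SD = √((8.7² + 9.9²)/2) = 9.32, so 7.5/9.32 = 0.805. As a paired effect size, the SD of the change is √(8.7² + 9.9² − 2r × 8.7 × 9.9). This is 9.36 at r = 0.5 and again gives 0.80. The correlation r is not in the article.

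**Step 2: the plan's own figure.** Paired t-test, noncentrality 0.80 × √n, n − 1 degrees of freedom, two-sided 5%: power is 79.0% at n = 14, 82.1% at n = 15 and 84.8% at n = 16. So 15 is the answer for this test. The alternatives do not give it: one-sided paired needs 12, two-sample two-sided needs 26 per arm, and two-sample one-sided needs 21 per arm.

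**Step 3: the between-arm comparison, unadjusted.** Two-sample t-test, noncentrality d × √(n/2), 2n − 2 degrees of freedom, two-sided 5%. At d = 0.80:
- 15 per arm: 56.2%
- 16 per arm: 59.1%
- 80% power needs 26 per arm

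**Step 4: the between-arm comparison with baseline-adjusted ANCOVA.** The residual SD shrinks by √(1 − r²), so the noncentrality is d/√(1 − r²) × √(n/2), with 2n − 3 degrees of freedom. Points are d × 9.32. With 16 per arm:

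| Analysis | Power at d = 0.80 | Power at d = 0.40 | d detectable at 80% | In points |
|---|---|---|---|---|
| Unadjusted | 59% | 19% | 1.02 | 9.5 |
| ANCOVA, r = 0.5 | 71% | 24% | 0.89 | 8.3 |
| ANCOVA, r = 0.6 | 78% | 28% | 0.82 | 7.6 |
| ANCOVA, r = 0.7 | 86% | 33% | 0.73 | 6.8 |

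The d = 0.40 column (0.40 × 9.32 = 3.7 points, about half the pilot gain) is an illustration only. The article gives no between-arm difference. The points are on the scale of the pilot's total score.

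**Step 5: comparison with the pilot.** The detectable difference is 9.5/7.5 = 127% of the whole pilot gain unadjusted, and 110%, 102% and 91% of it with ANCOVA at r = 0.5, 0.6 and 0.7. For a between-arm difference of that size, the no-Wii arm would have to gain almost nothing, or the Wii arm would have to gain far more than in the pilot.

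**The case against.** Three points can be made for the plan.

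First, the article is open about what it did. It calls the calculation within-group and names the Wii arm. A reader might infer that it claims 80% power for Wii versus no-Wii, but no sentence says so. The arithmetic is also right for the test used. This stands: the defect is a mismatch between the sizing and the trial's question, not a false statement or a calculation error. It does not cure the mismatch, because the article then treats the result as the number required in each group of a two-arm trial and offers no other justification.

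Second, Statistical methods names ANCOVA, so 59% need not be the operative figure. With baseline adjustment and a correlation of 0.7, power at d = 0.80 is 86%. This stands too, and it rules out the stronger reading that the trial is underpowered for d = 0.80 under any analysis. But neither the covariate nor the correlation is stated, and the non-parametric route falls back on an unadjusted test. If 0.80 is a true paired effect size, the pilot SDs imply r of about 0.5, which gives 71%.

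Third, a reader might infer that regression to the mean explains the pilot gain, since the trial selects children with low scores on the same test. The article does not say how the six pilot children were chosen, so this is a possibility and not a demonstrated fact. Likewise, no passage supports calling any particular between-arm difference the realistic one.

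**Conclusion.** The concern holds in this form: the trial is sized on a contrast other than the one it sets out to test, and the stated 80% does not carry over. At d = 0.80 and 16 per arm, between-arm power lies between 59% and 86%, depending on whether baseline is adjusted for and on a correlation that the article does not give. It reaches 80% only if that correlation is above about 0.6.

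Even the favourable end requires a between-arm difference about as large as the entire uncontrolled Wii gain, against an active, matched comparator. For clearly smaller differences, power is low under every analysis considered.

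The figures assume normal scores, a common SD of 9.32 taken from six children, 16 analysed per arm and a full two-sided 5% for this comparison. Any Bonferroni division of that 5% would lower them.

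**What to change.** Keep the number of children and rewrite the Sample size paragraph so that it:

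- states that 15 is the size for a pre-post change within the Wii arm, and that the 80% does not apply to Wii versus no-Wii;
- names as the primary analysis the between-arm comparison of the post-intervention MABC-2 total standard score, adjusted for its baseline value;
- gives the power of that comparison at d = 0.80 with 16 per arm (59% unadjusted; 71%, 78% and 86% with ANCOVA at r = 0.5, 0.6 and 0.7) and the detectable d (1.02; 0.89, 0.82 and 0.73), with r marked as an assumption;
- commits to reporting the between-arm difference with its 95% confidence interval, and says that a non-significant result will not be read as equal efficacy.

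The cost is one rewritten paragraph and a matching line in Statistical methods. No extra children are needed. The drawback is that the stated power becomes less favourable.

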### Randomization

Children will be randomly distributed by draw into one of the two training groups within a week at most after MABC-2 assessment. In case the draw leads to a sequence of four children in the same treatment group, the following four will be automatically allocated in the other. Once the distribution of blocks of four children is equalized, a new draw will be done for the following children to be randomly distributed. A person not involved with the study will receive a list of all children and will write in one piece of paper the term “Wii” and in another piece of paper the term “no-Wii.” This person will fold each piece of paper and will request to another collaborator not involved in this study to choose between the two papers. Then, following this draw, each child will be allocated into Wii or the no-Wii intervention group.

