Criteria D – The motor limitations showed by the children do not come from intellectual or visual impairment, or neurologic conditions such as cerebral palsy, dystrophy or any degenerative disease. In order to eliminate these associated conditions, school data about the children will be assessed, teachers will be interviewed and also physiotherapists will offer assessments in order to eliminate any sign of the mentioned neurologic conditions. In addition, psychiatric disorder history will be assessed through the parents’ interview as well as based on children’s forms at school in order to avoid the heterogeneous profile of those children. If we find children who have already received a psychiatric diagnosis (other than DCD) we will exclude them from the study. In addition, we will exclude children who may have undiagnosed psychiatric conditions but have recognizable contra-indications such as high levels of anxiety, impulsivity or attentional difficulties.

Highly anxious, inattentive or oppositional children who might be unable to complete either intervention program will be excluded from the study because they might find the interventions distressing. Children will be allowed to continue regular physical education classes at schools. Other concomitant care or interventions during the period of intervention will not be allowed.

In case any children are missed before the intervention ends, we use the intention-to-treat analysis.

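### After four children in a row enter one arm, the next four go to the other arm without a draw, so some allocations can be foreseen if allocation is sequential

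*Protocol article*

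**What the plan says.** The Randomization section describes the allocation in five steps.

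- **Timing:** "Children will be randomly distributed by draw into one of the two training groups within a week at most after MABC-2 assessment".
- **The draw:** an uninvolved person "will write in one piece of paper the term “Wii” and in another piece of paper the term “no-Wii", and a second uninvolved collaborator picks one. Each drawn child therefore has probability 1/2 for each arm.
- **The run rule:** when four children in sequence fall in one group, "the following four will be automatically allocated in the other".
- **The restart:** "Once the distribution of blocks of four children is equalized, a new draw will be done for the following children to be randomly distributed".
- **The list:** "A person not involved with the study will receive a list of all children".

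The Blinding section also places the draw with a professional outside assessments and interventions, and blinds assessors to group. The Design section says that the two protocols have different therapists. The Sample size section requires 15 per group and raises this to 16. No section shown caps the arms at 16 or ties their totals together.

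Patient population includes an exclusion that rests on judgement: "Highly anxious, inattentive or oppositional children who might be unable to complete either intervention program will be excluded from the study".

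**The concern.** An allocation is concealed if nobody who can influence entry can tell where the next child will go. The run rule removes chance from four consecutive allocations at a time, and what triggers it is easy to see. One arm plays console games and the other throws, bowls and balances with real equipment, under different therapists, so staff and families know who went where. The rule itself is published.

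A person who knows that the last four children entered one arm can predict the next four with certainty. Such a person might bring a child forward, hold one back, or read the behavioural exclusion more or less strictly. In a trial of 32 children, a few placements of this kind could shift the comparison of MABC-2 scores, and no later analysis could reliably undo it. The four forced children also share one arm and neighbouring calendar time.

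**Working it through.** **Inputs.** Fair two-slip draw, run length four, forced block of four, then drawing restarts (Randomization). Total of 32 children, reading the 16 in Sample size as per group. The article gives no figure for the forced share or for balance, so there is none of its own to reproduce here.

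**Plain reading.** Any run of four triggers the rule, and the run counter returns to zero after the forced four.

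- *Long-run share.* The expected number of fair draws to reach four alike in a row is 2^4 − 1 = 15. Each cycle then adds 4 forced children, so the share is 4/(15 + 4) = 4/19 = 21.1%.
- *Share for 32 children.* The trial starts with no run and may end within a cycle, so the share is lower. Exact enumeration over arm count, current run and forced places left gives 5.94 forced, and 5.94/32 = 18.6%. A simulation of 200,000 trials gives 5.95.
- *At least one forced child.* This happens unless the first 31 children contain no run of four, which has probability 0.092. So 1 − 0.092 = 0.908, or about 91% of trials.

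**Other readings of the rule, 32 children.**

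| Reading | Mean share forced | At least one forced | Exact 16:16 |
|---|---|---|---|
| Any run of four, counter resets | 18.6% | 90.8% | 24.9% |
| Checked only on consecutive groups of four | 9.9% | 60.7% | 19.9% |
| Forced children count towards the next run | 27.1% | 90.8% | 27.5% |

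In the second row, a group of four is all alike with probability 2/16 = 1/8. With eight groups, no child is forced only if none of the first seven is alike: (7/8)^7 = 0.393, and 1 − 0.393 = 0.607. In the third row, the first forced block arises exactly as in the first row, so that probability is unchanged.

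**Balance.** On the plain reading, the arms differ by 4 or more (18:14 or worse) in 34.0% of trials and by 6 or more (19:13 or worse) in 11.0%. Under simple randomisation of 32 children, 16:16 occurs in 14.0% and 18:14 or worse in 59.7%. The run rule therefore improves balance without securing it.

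**Power cost of imbalance.** This uses a two-sample t-test, two-sided alpha 5%, with a standardised difference of 0.80 between arms. That value is an assumption: it borrows the article's within-group effect size. The noncentrality is 0.80 × √(n1·n2/(n1 + n2)).

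| Split | Noncentrality | Power |
|---|---|---|
| 16:16 | 2.263 | 59.1% |
| 18:14 | 2.245 | 58.4% |
| 19:13 | 2.223 | 57.6% |

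The loss is 0.7 percentage points at 18:14 and 1.5 at 19:13.

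**Can the forced places be foreseen?** One sentence has a person receive a list of all children, which could mean a list closed before any draw. Another allocates "within a week at most after MABC-2 assessment". MABC-2 is also a screening instrument, taking 30 to 40 minutes per child, for children recruited across public and private schools. A single closed list would need every included child to be assessed within about one week of the draw. Sequential or small-batch allocation is the more natural reading, but the text does not settle it.

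**The case against.** The best reply is that people outside the study make the draw and assessors are blinded. If the list is complete before drawing starts, a forced place cannot influence who enters. This stands in part. A closed list would remove the route to steering enrolment. However, the independence of the drawer conceals nothing where there is no draw, and blinding assessors does not hide past assignments from therapists or from those who recruit.

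A second reply is that the forced share alone proves little. Fixed permuted blocks of four, a standard method, leave (1 + 1/3)/4 = one third of allocations determinate to someone who knows the block size and the history. This is correct. The objection to the run rule is that its trigger is published and visible and that it fixes four places at once. Randomly varying block sizes largely avoid this.

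A third reply is that steering is inferred. The Design section says that children who meet the inclusion criteria are then allocated, so exclusion should come first, and nothing says that staff who know the sequence decide exclusions or control the order of entry. This also stands: the article shows an opening, not its use.

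A reader might infer three stronger things that the document does not support:

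- *That a fifth of allocations are simply known in advance.* The share depends on the reading, and foresight needs sequential entry plus knowledge of the rule and of the last four assignments.
- *That concealment is lost outright.* It is lost only under those conditions.
- *That failing to secure 16:16 costs important power.* The loss is about one percentage point, and the rule balances better than simple randomisation does.

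**Conclusion.** The point holds as a conditional weakness that can be avoided. The stated rule places about 19% of 32 children without a draw on the plain reading, within a range of about 10% to 27%, and on the plain reading it operates at least once in about 91% of trials. Those places can be foreseen by anyone who knows the rule and the last four assignments, provided that allocation is sequential or in small batches, as the timing sentence suggests.

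The figures assume 32 children and fair draws. The article gives no basis for estimating the size of any resulting bias, and none is claimed. Imbalance between the arms is a side effect with negligible cost and does not carry the argument. The rule should be changed, but it does not by itself invalidate the design.

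**What to change.** Delete the run-of-four rule and the per-child paper draw. Have the same uninvolved person generate one computer list in permuted blocks of randomly varying size (for example 2, 4 and 6), totalling 16 per arm, and keep both the list and the block sizes from recruiting and treating staff. Release each assignment only after that child's eligibility, including the behavioural exclusion, and baseline MABC-2 are recorded. State whether children are allocated one at a time or from a closed list.

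The cost is one list generated once by a person already in the plan, and a short amendment. With a fixed total of 16 per arm, the last place or places can still be deduced by someone who has kept count, which is a much smaller exposure than repeated forced runs of four.
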